### Randomisation

Study participants will be randomised strictly sequentially, as they become registered as eligible for randomisation on the telephone system. The treatment group will be allocated by computer using a minimisation algorithm and stratification by centre and laterality (one or both Achilles tendons affected) following a call to a secure, centralised, telephone-based randomisation service. Allocation concealment will be maintained by an independent randomisation team who will be responsible for generation of the sequence and will have no role in the allocation of participants. The randomisation system will allocate each participant a unique trial number.

Stratification by centre will help ensure that any clustering effect related to the centre itself will be equally distributed in the trial arms. Stratification on the basis of bilateral presentation will also be implemented to account for the poorer outcome associated with this sub-population.

### Post-randomisation withdrawals

Participants may withdraw from the trial treatment and/or the trial at any time without prejudice. Unless a participant explicitly withdraws their consent, they will be followed-up wherever possible and data collected as per the protocol until the end of the trial. For participants explicitly withdrawing consent for follow-up procedures, trial data obtained up until the point of withdrawal will be included in the final analysis.

### Interventions

#### Pre-injection

The PI at each site will identify relevant healthcare professionals to be trained and will record those who have completed training on the delegation log. Only those individuals listed on the delegation log will be allowed to prepare and administer trial interventions. At each centre the trial training programme will be delivered and documented by the chief investigator ([name]) and WCTU trial manager.

Following consent, completion of baseline questionnaires and randomisation, all participants will have approximately 10 mL of whole blood withdrawn from the antecubital fossa (vein at the elbow) and 5 mL of 2% lignocaine (local anaesthetic) will be injected into the skin overlying the painful tendon area for pain relief; this will be done with the participant in the prone (lying down and facing away) position on a treatment couch.

#### PRP injection procedure

The whole blood will be centrifuged using the study specific Glo PRP system (Glofinn). Each centre will be supplied with the same centrifuge system to facilitate standardisation of the intervention.

Although treatment in the prone position means that the participant will be facing away from the healthcare professional, the syringe will be masked to make sure that the participant cannot see the contents of the syringe. Participants will then have one injection of the prepared platelet layer (approximately 3 mL) injected into the Achilles tendon using a standard ‘peppering’ technique at the site of the tendon pain. This technique involves a single skin portal and then five penetrations of the tendon.

#### Placebo injection procedure

For the placebo injection, the masked needle will be inserted under the skin, but not into the tendon. The participant will feel the needle but nothing will be injected. There is an active debate pertaining to the treatment effect of needling trauma,^10^ or the trauma of injecting fluid directly into the tendon. Therefore following discussion with the trial steering committee (TSC) and the data monitoring and safety committee (DSMC) a decision was made that a true placebo arm would need to avoid these possible treatment effects. The group consensus was therefore not to administer the placebo injection intratendinously and under the skin only. At the 6 months time point, following completion of all data collection, participants will be asked if they think they know their treatment allocation or not.

#### Post-injection

After both the PRP and placebo treatments all participants will receive the same post-injection advice sheet. The post-injection advice sheet will inform participants that they may have increased pain for 24–48 hours, after which period they can resume their normal activities as pain allows. It will also include advice on potential adverse events (eg, infection and reddening of the skin) and what to do if they occur. Participants will be instructed not to undergo any further interventions for a period of 6 months, which will be monitored at each follow-up time point.

#### Bilateral presentations

The index tendon will be randomised and managed accordingly. Regarding the non-index tendon the participant will have two options, to have no treatment or to receive a second injection into the non-index tendon.

#### Technical failure

In the unlikely event that the project specific centrifuge system fails once blood has been drawn for PRP preparation/Placebo preparation the patient will be allocated to the placebo arm and analysed as a protocol violation.

### Quality assurance

Quality assurance checks will be carried out by a member of the trial team to assess compliance with the earlier intervention preparation and delivery. These checks will be done face to face and remotely using recording devices. Any deviations noted from the outlined trial interventions will be monitored by the oversight committees. If required, further training will be implemented to resolve any inconsistencies.

Additional quality assurance procedures to verify the quality of the PRP preparation will include research nurses from participating trial sites preparing PRP samples from healthy volunteers. Healthy volunteers will be recruited internally from these trial sites through advertisement in routinely distributed newsletters and posters. All volunteers will receive a screening phone call to be considered and only excluded if they have presence of systemic conditions (including diabetes, rheumatoid arthritis, peripheral vascular disease); they are pregnant and/or breastfeeding; use of anticoagulant therapy (warfarin, dabigatran, heparin) or are unable to adhere and consent to procedures.

Following consent procedures, healthy volunteers will provide two blood samples of up to 10 mL. Sample 1 will be kept as a whole blood control sample for analysis and sample 2 will be processed by the trial research nurses to produce a PRP sample for analysis. Samples will be anonymised and transported to an independent test lab which will conduct cell counts of whole blood and PRP preparations. Red cell, platelet and white cell counts (with full differential count) using a blood counter will be undertaken. All samples will be destroyed after analysis.

### Blinding

It will not be possible to blind the research or clinical team involved in treatment preparation or delivery due to the nature of the intervention. All participants will be blinded and not know their treatment allocation through masking of the treatment syringe to prevent them from seeing the contents, as well as by being face-down during the injection. Participants in both groups will wait for approximately 30 min (PRP preparation time), and not be in the same room as the centrifuge. If this is not possible the participant will lie in the prone position and the centrifuge will spin without any PRP being prepared.

### Adverse event management

Adverse events will be listed on case report form for return to the ‘ATM’ office. Serious adverse events (SAEs) will be entered onto the SAE reporting form and reported to the central study team. All SAEs that occur between date of randomisation and the 2-week follow-up point will be followed-up as per protocol until the end of the trial. All SAEs will be reported to the sponsor (University of Warwick), ethics committee and oversight committees.

### End of trial

The trial will end when all participants have completed their 6-month follow-up. The trial will be stopped prematurely if mandated by the ethics committee, following recommendations from relevant oversight committees or funding for the trial ceases. The research ethics committee will be notified in writing within 90 days when the trial has been concluded or within 15 days if terminated early.

### Trial oversight

The trial management group (TMG) will meet monthly and consist of the project staff and co-investigators responsible for the day-to-day running of the trial. The TMG will report to an independent TSC who will hold meetings not less than once a year and take responsibility for approval of the protocol, monitoring and supervising the progress of the trial and considering recommendations from the DSMC. The TMG will also report to the independent DSMC, who will hold meetings not less than once a year. Confidential reports containing recruitment, protocol compliance, safety data and interim assessments of outcomes will be reviewed by the DSMC.

### Patient and public involvement (PPI)

PPI members have been active members on the TMG and TSC, and have reviewed all study materials. At the end of the study they will be contributing to dissemination plans distributed through the trial website and other relevant platforms.

### Statistical methods

The primary analysis will compare the VISA-A score at 6-month follow-up between the two treatment groups on an intention-to-treat (ITT) basis. Mixed-effects linear regression will be used with adjustment for design factors (centre and laterality), age, sex and baseline VISA-A score. Centre will be taken as a random effect to allow for possible heterogeneity in patient outcomes. Mean difference with 95% CI will be reported. Data transformation will be applied to the outcome before the modelling if VISA-A at 6 months is non-normally distributed. A p value<0.05 will be considered statistically significant.

The secondary analysis compares the outcomes including VISA-A at 3 months, EQ-5D-5L VAS and index scores at 3 and 6 months and pain VAS and complication rate at 2 weeks, 3 and 6 months. They will be analysed by ITT using linear regression with and without adjustment for design factors and baseline data. In addition, VISA-A at 6 months will be analysed in the following ways: (1) unadjusted linear regression by ITT and (2) adjusted mixed-effects regression by per-protocol to assess the impact of non-compliance. Kaplan Meier plot will be used to compare the time to complication by treatment if sufficient number is observed in each complication class. In case of bilateral tendinopathy (both sides), one randomly select side will be included in the analysis. Although missing data are not expected to be a problem for this study, the missing mechanism will be assessed and imputation may be used when deemed appropriate. The imputed data will be used for a sensitivity analysis. Pre-specified subgroup analysis include laterality (single vs bilateral) and duration of symptom (≤median vs>median duration). The analysis will be adjusted in the same way as the primary analysis. A detailed analysis plan will be finalised prior to final data lock.

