## Research question

In adults with painful mid-substance Achilles tendinopathy lasting longer than 3 months, does a single injection of PRP (intra-tendinous injection with a peppering technique) improve VISA-A scores by a minimum of 12 points when compared with a placebo (subcutaneous injection of a dry needle and no peppering technique) injection at 6-month post-injection?

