### Sample size

The primary outcome for the study is the VISA-A score^14^; it has a range between 0 and 100, a lower score indicating more symptoms and greater limitation of physical activity and 100 being asymptomatic. The minimum clinically important difference for the VISA-A score is estimated to lie between 10 and 12 points.^11 12^ From our previous feasibility publication,^3^ VISA-A scores were observed to be approximately normally distributed with a SD of 26. If the true difference between the experimental and control treatment group means is 12 points, a sample of 100 patients in each group will be required to reject the null hypothesis (population means of the experimental and control groups are equal) with probability 0.9 (90% power). This equates to an effect size of 0.46, which we would consider to be moderate. The type I error rate (significance level) associated with this test is 5%. Allowing approximately 15% loss to follow-up, this amounts to 240 patients in total.

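### The rule to transform 6-month VISA-A if it is non-normal would remove the mean difference in points that the trial is designed and powered to report

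*Protocol article*

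**What the plan says.** In the Statistical methods section of the protocol article, the primary analysis is fixed as follows: "The primary analysis will compare the VISA-A score at 6-month follow-up between the two treatment groups on an intention-to-treat (ITT) basis". The model is then named: "Mixed-effects linear regression will be used with adjustment for design factors (centre and laterality), age, sex and baseline VISA-A score", with centre as a random effect. The effect measure comes next: "Mean difference with 95% CI will be reported". The sentence directly after that reads: "Data transformation will be applied to the outcome before the modelling if VISA-A at 6 months is non-normally distributed".

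The rest of the design is in VISA-A points. The Research question section asks whether PRP will "improve VISA-A scores by a minimum of 12 points when compared with a placebo" injection. The Sample size section starts from the same quantity, "If the true difference between the experimental and control treatment group means is 12 points". It sets a null hypothesis of equal population means, an SD of 26, and a minimum clinically important difference of 10 to 12 points on a scale bounded at 0 and 100.

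The article does not say that a raw-scale adjusted estimate stays primary if the outcome is transformed.

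**The concern.** The rule lets the observed outcome data decide the scale of the primary analysis. Three problems follow.

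- **The effect measure changes.** After a nonlinear transformation, the treatment coefficient is not a difference in mean VISA-A points. It cannot be set against the 12-point target or the 10-12 point important difference, or pooled with trials that report points. Back-transforming does not in general recover the difference in means; a log scale, for instance, gives a ratio of geometric means.
- **The hypothesis changes.** The sample size is built to reject equality of means. Equality of means on a transformed scale is a different hypothesis, and the two can disagree.
- **The check looks at the wrong quantity.** A linear mixed model makes its distributional assumption about residuals given treatment, baseline score and the other terms. It makes none about the marginal distribution of the outcome.

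At stake is whether the primary estimate can answer the trial's stated question.

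**Working it through.** **1. The plan's own figure, to fix its scale.** Inputs from the Sample size section: difference 12, SD 26, power 90%, alpha 5% (two-sided assumed, since sidedness is not stated), loss about 15%.

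- n per arm = 2 × (1.960 + 1.282)² × 26² / 12² = 98.7, so 99. A two-sample t-test calculation gives 99.6, so 100, as stated.
- Standardised effect: 12 / 26 = 0.46, as stated.
- Power with 100 per arm: 90.4% (normal approximation) or 90.1% (t-test).
- Loss to follow-up: 200 / 0.85 = 235.3, so 236. The stated 240 allows 1 − 200/240 = 16.7%, which fits approximately 15%.

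The sample size is correct, and it is the sample size for a difference in means on the raw scale.

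**2. What a transformed effect means in points.** Take a reflected log, log(101 − score), as one example; the article names no transformation. A 12-point gain from 50 to 62 gives a ratio of (101 − 62)/(101 − 50) = 39/51 = 0.765. The gain in points for that same ratio is (101 − start) × (1 − 0.765):

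| Starting score | Gain in points |
|---|---|
| 30 | 16.7 |
| 50 | 12.0 |
| 70 | 7.3 |
| 85 | 3.8 |

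Conversely, a fixed 12-point gain becomes ln(61/49) = 0.22 from a score of 40, ln(41/29) = 0.35 from 60, and ln(21/9) = 0.85 from 80. No single value in points corresponds to the transformed coefficient.

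**3. Whether the null hypothesis survives.** Two arms were simulated with equal means of 60 but SDs of 26 and 20 (scaled beta, 100 per arm; shapes and second SD assumed). The raw-scale Welch test rejected in about 5% of runs and the reflected-log test in 26-27%. The transformed test is then not a test of equal mean VISA-A.

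**4. How likely the rule is to fire.** With SD 26, a normal distribution with mean 55 has an upper 97.5% point of 55 + 1.96 × 26 = 106, beyond the scale's maximum. The article gives no criterion, so a Shapiro-Wilk test at 5% on 200 pooled scores was used as one possible reading, at means of 55, 65 and 75:

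| Assumed shape | Share of runs rejecting normality |
|---|---|
| Beta, SD 26 | 100% at each mean |
| Normal clipped to 0-100, SD 26 before clipping | 89% to 100% |
| Normal clipped to 0-100, SD 20 before clipping | 4% to 100%, rising with the mean |

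**5. Whether the untransformed analysis needs rescue.** Scaled beta scores were simulated with SD 26, control means of 50, 60 and 70, 100 per arm, 20,000 runs and an unadjusted t-test:

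- type I error 4.9-5.2%;
- power for 12 points 89-90%;
- coverage of the 95% interval for the difference in points 94.8-95.2%.

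In the same runs the reflected-log test rejected more often when the true difference was 12 points: 92%, 98% and over 99% at control means of 50, 60 and 70. So a transformed test can gain power under such shapes. It does so for the different hypothesis shown in step 3, and without an estimate in points.

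**The case against.** The rule is conditional, and the sentence before it promises a mean difference without condition. One could read the two together as keeping the point-scale result beside a transformed model. The secondary unadjusted intention-to-treat regression of 6-month VISA-A may also remain on the raw scale. A detailed analysis plan is promised before final data lock, and it could name the transformation, the trigger and a back-transformation. The article reports pilot scores as approximately normal and the instrument as free of floor and ceiling effects. The simulated beta shapes, especially at means of 65 and 75, pile up at 100 and so sit badly with that. Finally, the type I error of the two-stage rule itself was not simulated.

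Much of this is fair on detail. How often the rule fires depends on the assumed shape, mean and SD, and on whether normality is judged by a test or by eye. The missing transformation and criterion are matters for the analysis plan and are not the fault here. No inflation of type I error by the rule as a whole has been shown. A worst-case choice of the smallest p value among five scales gave about 9%, but nothing in the article says that would be done.

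The central point stands. The article says the transformation will be applied before the modelling, so the adjusted primary model would be fitted to the transformed score. The unadjusted analysis has no stated scale and is not the primary analysis.

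**Conclusion.** The concern holds. A rule that the article states as a commitment conflicts with its own effect measure, research question and sample size. If the 6-month scores are judged non-normal, the primary estimate will not be a difference in VISA-A points and cannot be compared with the 12-point target. In the reflected-log example, one coefficient spans 16.7 to 3.8 points over starting scores of 30 to 85.

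The conflict does not depend on how often the rule fires. That firing is likely does rest on an SD near 26 and a formal test. That the untransformed comparison is adequate rests on assumed beta shapes and an unadjusted t-test with about 100 per arm. The demonstrated harm is to the estimand and its interpretation. Because it concerns the primary result, it should be corrected before the outcome data are examined.

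**What to change.** Delete the transformation sentence and replace it with three statements:

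1. The primary result is the adjusted mean difference in untransformed 6-month VISA-A, in points with a 95% CI, from the mixed model already specified, whatever the distribution of the scores.
2. Model adequacy is judged on residuals. If they are clearly non-normal or heteroscedastic, a bootstrap interval or robust standard errors are reported as a sensitivity analysis.
3. Any analysis of transformed scores is a sensitivity analysis and does not replace the primary result.

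The same wording should go into the statistical analysis plan. The cost is a short change of text and, if needed, one bootstrap run. The sample size stays at 100 per arm and 240 in total, with about 90% power for 12 points.

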### Secondary objectives

To quantify and draw inferences on observed differences in the VISA-A score at 3-month post-randomisation.To identify any differences in health-related quality of life measurement (HRQoL) between trial treatment groups at 3-month and 6-month post-randomisation.To identify any differences in pain measurements between trial treatment groups at 2-week, 3-month and 6-month post-randomisation.To report the complication profile of PRP injections at 2-week, 3-month and 6-month post-randomisation.

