#### Secondary

Euro-Qol 5 Dimensions Score (EQ-5D-5L^16^) is a generic, validated, cross-disciplinary standardised health utility instrument widely used to assess HRQoL. It has two parts, a visual analogue scale (VAS), which measures self-rated health, and a health status instrument, which will be the focus of this study, consisting of a five-level response (no problems, slight problems, moderate problems, severe problems and extreme problems) for five health domains related to daily activities: (i) mobility, (ii) self-care, (iii) usual activities, (iv) pain and discomfort and (v) anxiety and depression. The five dimensions are combined together to provide a 5-digit number that describes the individual’s health state. The 5-digit responses, from the EQ-5D health classifications, are converted into an overall score using a published utility algorithm for the UK population.^17^ It has good test-retest reliability, is simple for participants to use and gives a single preference-based index value for health status that can be used for broader cost-effectiveness comparative purposes.^18^ These data will be collected at baseline, 3 and 6 months after randomisation.

Pain is assessed using a VAS comprising of a horizontal 10 cm line in length, anchored by two verbal descriptors (no pain and worst imaginable pain) to indicate a participant’s pain level on the day on completing the questionnaire.^19^ These data will be collected at baseline 2 weeks, 3 and 6 months after randomisation.

Participants will be asked if they have experienced any complications during follow-up data collection at 2 weeks, 3 and 6 months after randomisation. Complications expected and related to the study treatment that are collected at the specified time points consist of bruising and discomfort at the venesection site, syncopal (fainting) episode associated with venesection or tendon injection, infection, mild discomfort and bleeding at the injection site, swelling, skin discolouration and allergic reaction.

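### Linear regression is assigned to the yes/no complication outcome; its 95% CI is sound at rates of about 5% or more but can be far too narrow for rare, unequal complication classes

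*Protocol article*

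**What the plan says.** The Statistical methods section of the protocol article names as secondary comparisons VISA-A at 3 months, the EQ-5D-5L scores, and "pain VAS and complication rate at 2 weeks, 3 and 6 months". The next sentence covers them all: "They will be analysed by ITT using linear regression with and without adjustment for design factors and baseline data". The only other method given for complications is graphical: "Kaplan Meier plot will be used to compare the time to complication by treatment if sufficient number is observed in each complication class".

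On data collection, the Secondary part of Outcome measures says: "Participants will be asked if they have experienced any complications during follow-up data collection at 2 weeks, 3 and 6 months after randomisation". The classes listed there include venesection-site bruising, fainting, and "infection, mild discomfort and bleeding at the injection site, swelling, skin discolouration and allergic reaction". Adverse event management adds a second route: "Adverse events will be listed on case report form for return to the ‘ATM’ office". Neither section mentions onset dates, and no expected complication rate appears anywhere.

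The related secondary objective is "To report the complication profile of PRP injections at 2-week, 3-month and 6-month post-randomisation".

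**The concern.** Whether a participant had a complication is a yes/no outcome. Ordinary linear regression uses one pooled residual variance and a t quantile. That suits the continuous scores in the list, but it can break down for a proportion near zero. With no events in either arm, the estimated variance is zero and so is the width of the interval.

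This concerns a method the article states, not a detail left out. The complication profile is a secondary objective, and several listed classes (infection, allergic reaction, fainting) may be uncommon. For those classes the interval is the main result: it tells the reader how large a difference in harm remains compatible with the data. An interval that is too narrow gives false reassurance.

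The plot raises a separate, conditional question. If the only timing information is the contact at which a complication was reported, a Kaplan-Meier curve steps at the contacts.

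**Working it through.** **Arm size.** The only stated figure that bears on this is the sample size. The Sample size section gives a 12-point difference, SD 26, 5% significance and 90% power. With a two-sided test, n = 2(1.960 + 1.282)² × 26² / 12² = 98.6, so 99 per arm; the t-test version gives 99.6, so 100, as stated. Allowing 15% loss, 200 / 0.85 = 235.3, so 236, against the stated 240. Complications would therefore be compared with about 100 (followed up) to 120 (randomised) per arm.

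**Method.** For event counts x₁ and x₂ with n per arm, p̂ = x/n and d = p̂₁ − p̂₂:
- Linear regression CI: d ± t × SE, where SE² = [n p̂₁(1−p̂₁) + n p̂₂(1−p̂₂)] / (2n−2) × (2/n), and t is 1.972 (n = 100) or 1.970 (n = 120).
- Comparator: the Newcombe-Wilson interval for a risk difference.
- Coverage: the sum of binomial probabilities over all (x₁, x₂) whose interval contains the true difference. This is exact, not simulated.

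**Coverage of the nominal 95% CI.** True rates are assumed.

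| True rates | Linear, n=100 | Newcombe, n=100 | Linear, n=120 | Newcombe, n=120 |
|---|---|---|---|---|
| 30% v 10% | 95.0% | 95.1% | 94.9% | 95.1% |
| 5% v 5% | 95.6% | 96.4% | 95.4% | 96.1% |
| 10% v 2% | 94.8% | 96.5% | 94.3% | 96.0% |
| 5% v 1% | 92.9% | 97.2% | 92.4% | 96.8% |
| 3% v 0.5% | 93.3% | 98.9% | 87.2% | 98.0% |
| 2% v 0.5% | 86.4% | 99.6% | 90.5% | 99.2% |
| 1% v 1% | 98.7% | 99.7% | 98.0% | 99.5% |
| 0.5% v 0.5% | 99.8% | 100.0% | 99.6% | 100.0% |

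Across all pairs tested at 100 per arm, the Newcombe-Wilson interval never fell below 94.9%.

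**Why it fails at 2% v 0.5%, n = 100.** The true difference is 1.5 points. The 2% arm has no events with probability 0.98¹⁰⁰ = 13.3%, and the linear interval then misses:
- 0 v 0: SE = 0 and the interval is the single point 0. Probability 0.98¹⁰⁰ × 0.995¹⁰⁰ = 0.1326 × 0.6058 = 8.0%.
- 0 v 1: d = −1.0 point, SE = 1.0 point, upper limit −1.0 + 1.972 × 1.0 = 0.97 points, below 1.5.

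For 0 v 0 the Newcombe-Wilson limits are ± z²/(n + z²) = 3.84/103.84 = ± 3.7 points.

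**Why it fails at 3% v 0.5%, n = 120.** The true difference is 2.5 points. With 1 v 0, d = 0.833 and SE = 0.833 points, so the upper limit is 0.833 + 1.970 × 0.833 = 2.47, a narrow miss. The 3% arm has no events with probability 0.97¹²⁰ = 2.6% and one event with probability 120 × 0.03 × 0.97¹¹⁹ = 9.6%, together 12.2%. Coverage in this range is therefore erratic: a small change in n or in the rate moves it by several points.

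**Type I error.** For equal rates of 0.5%, 1%, 2%, 5%, 10% and 20% at 120 per arm, unadjusted linear regression rejects in 0.4%, 2.0%, 4.4%, 4.6%, 5.0% and 5.1%. The maximum over rates up to 50% is 5.2% (5.6% at 100 per arm).

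**Adjusted model.** In a simulation (200 participants, 3000 runs, covariates unrelated to outcome), coverage was 94% to 95% for rates from 2% v 3% to 20% v 40%. Between 14% and 17% of fitted risks were negative at 2% v 3% and 2% v 7%. The worst pairs in the table were not simulated with adjustment.

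**Timing.** Reports at 2 weeks, 3 months and 6 months place an undated event in one of three intervals, the widest about 3 months.

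**The case against.** The strongest reply is that linear regression on a yes/no outcome in a 1:1 trial estimates the risk difference, which is the measure one would want, and does so well at ordinary rates. That stands. A reader might infer that the safety comparison would have wrong error bars in general; the table does not support this. Nor does the article say that complications are rare. Bruising, mild discomfort and swelling may be common, and so may the overall rate. The negative fitted risks did not spoil coverage of the treatment effect in the simulated scenarios.

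A reader might also infer that linear regression would signal harm the data do not support. With 120 per arm, 4 v 0 events gives p = 0.044 by linear regression and 0.12 by Fisher's exact test; 5 v 0 gives 0.024 and 0.060; 7 v 1 gives 0.031 and 0.066. These gaps mainly reflect Fisher's conservatism: its type I error at equal rates of 1% and 5% is 0.1% and 2.1%. Barnard's exact test gives 0.045, 0.025 and 0.036, close to linear regression. Moving to Fisher would reduce sensitivity to harm.

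On the plot, it is fair to say that it is descriptive and is drawn only when a class has enough events. Adverse events are also listed on a case report form, and an article may well omit that onset dates are recorded. The documents therefore do not show that the plot would be misleading. The condition on event numbers, however, deals with sparse counts and not with undated events.

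Finally, the objective is worded as reporting, and a detailed analysis plan is to follow and may correct the sentence. That lowers the severity. It does not remove the point, because the article names a method for this outcome and the method is unsuitable for part of it.

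**Conclusion.** The point holds in a limited form. The article commits a yes/no outcome to linear regression. At about 100 to 120 per arm this is harmless where both rates are about 5% or more. Where one arm is at roughly 3% or less and the arms differ, the nominal 95% CI can fall to about 86% to 87% coverage. Where both arms are very rare it over-covers, as the Newcombe-Wilson interval also does, so under-coverage is the reason to change. Type I error stays at or below about 5%, apart from a maximum of 5.6% at 100 per arm.

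The size rests on assumed rates and on the unadjusted model; if no class is rare, nothing material changes. The Kaplan-Meier point depends on onset dates not being recorded, which the article does not settle. Severity is small to moderate: a secondary safety outcome, but a stated objective with a nearly free correction.

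**What to change.** 1. Limit the linear-regression sentence to the continuous outcomes: VISA-A, the EQ-5D-5L scores and pain VAS.
2. For complications, report the number and percentage of participants with at least one event, overall and by class, in each arm, with the risk difference and a score-type 95% CI such as Newcombe-Wilson. Use logistic regression adjusted for the design factors only where counts allow.
3. State whether onset dates are recorded. If they are, the Kaplan-Meier plot can stay; if not, show cumulative proportions at 2 weeks, 3 months and 6 months.

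The cost is wording in the analysis plan, with no new data. The small downside is that score intervals are conservative for very rare events (97% to 100% coverage at 100 per arm where one arm is at 0.5% to 2% and the other at 5% or less).
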